Appendix A: Risks and Benefits

Risks

There are less than minimal risks associated with this study.

While there could be concerns about allergic or other physical reactions by children to the peanut butter or soy, many studies in developing countries have found no such risk. There has been no indication of negative reactions to the food, allergy or otherwise, in other studies conducted around the world (Ghana, Malawi, Niger, etc.).  Infants and children in Haiti widely consume "mamba" or peanut butter without any adverse health consequences. A randomized controlled trial previously approved the National Bioethics Committee of Haiti (No 1011-23) and Human Research Protection Office (HRPO) of Washington University in St. Louis (IRB ID# 201101760) is testing the efficacy of a similar fortified peanut-butter paste, Nutributter. Among the 410 infants receiving this food, no peanut allergy has been identified.

In the Vita Mamba school feeding study, we will follow the same protocol to ensure there is a similar situation among school-age children in Haiti. When the fortified peanut-butter paste food is given for the first time, children will be monitored for any adverse reactions (itching, redness, rash, swelling, or difficulties in breathing) over a one-hour period. If a child reacts to the food, they will be treated immediately and become ineligible to continue in the study. For the remainder of the study, each school will be equipped with norepinephrine and diphendyramine (antihistamine) medication in case of allergic reactions at any time during the intervention period.

The measures of nutritional status are of minimal risk to the children. The finger prick associated with the Hemocue hemoglobin test will be no more painful than a vaccination shot, which children receive frequently. The study team will follow strict hygienic protocol with latex gloves and sterile equipment for the finger prick and handling of the samples.

Benefits

The direct benefits to the child will be decreased likelihood of nutrient deficiencies and improved health. Interventions that target prepubescent children have been shown to decrease the prevalence of nutritional deficiencies and improve school performance and overall child health (Soemantri, Pollitt, & Kim, 1985; Grantham-McGregor & Ani, 2001). Access to high quality, nutritious foods during the school day can boost enrollment, improve cognitive development, and increase performance measures on school exams (Soemantri, Pollitt, & Kim, 1985; Grantham-McGregor & Ani, 2001; Seshadri & Gopaldas, 1989). School feeding programs have also been shown to increase memory and the speed of processing by alleviating short-term hunger (Simeon & Grantham-McGregor, 1989).

The results of the study will demonstrate the effectiveness of using a lipid-based Ready-to-Use Supplementary Food (RUSF) as part of a school feeding program. While school feeding programs have been studied around the world, this study is among the first to examine a lipid-based RUSF in school-age children. It is intended to treat poor nutrition among school-age children on a population level with the possibility of long-term positive health and economic outcomes for the community. School feeding and increased enrollment have a positive influence on the economy and public health, which can be passed onto the next generation. The Government of Haiti is directly involved in this study and intends to use the results for future policy and programming in the country.

The new study in a rural area with the modifications described also allows the investigation of interventions to prevent anemia and promote growth with local products. The new study also allows us to test the RUSF against a strategy based on food.

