**Methodology**

**Study Design**. A quasi-experimental evaluation design is planned for this project.  Three primary schools will be matched on socio-economic and demographic factors and randomized into two participant groups:

*Group 1* (Control): Children 3-16 years of age in a school that does not normally participate in a school feeding program and will receive no food-based intervention during the study period. Deworming with Albendazole administered.

*Group* *2* (Vita Mamba): Children 3-16 years old in a school that does not normally participate in a school feeding program and who will receive Vita Mamba during the study period. Deworming with Albendazole administered.

**Study Activities**. This project will take place in schools in a communal section of the Terrier Rouge zone. This is a quasi-experimental study that will be coordinated by Washington University in St. Louis (WUSTL) in partnership with Meds & Food for Kids (MFK), Haiti’s National School Lunch Program (le Programme National de Cantine Scolaire, PNCS) and the Ministry of Public Health and Population (MSPP). There are three phases of the project: 1) planning, 2) intervention and 3) reporting and dissemination of findings.

Planning & Recruitment Phase. In the planning phase, there will be three primary activities: recruitment of staff and participants; training the study team; and program organization.

The Study Coordinator will be hired and begin work in September 2014. Two enumerators will be hired in October 2014. With the Principal Investigator, the coordinator will recruit and train the enumerators during the planning phase. The Study Coordinator will work with school personnel to enroll families of schoolchildren aged 3 to 16 years.

Parents/caregivers of eligible students will be acquainted with the study methods and procedures and will be asked to sign an informed consent form, which will be presented in the local languages (French and Creole). If parents/caregivers are unable to read, the consent form will be reviewed in full by French and Creole speaking trained enumerators to ascertain that the parent/caregiver has understood the nature of the study and is voluntarily enrolling their child in the study. A simple script will be reviewed with the students participating in the study to explain the RUSF product and the purpose of the anthropometric measurements and acceptability study.

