• Allergy to peanuts or soy;

• Fever or congenital or major health condition affecting the child;

• Child severely malnourished (weight-for-height Z score <-2).

Once eligibility is established, parents/caregivers will go through the informed consent process individually. The study staff will provide the children with a verbal description of the study, which will explain the purpose of the study, their role in the study and what to expect during the data collection methods. The children will be asked to give verbal assent. Following this, parents will be asked to return to the school on a scheduled date and the baseline survey will be administered.

**Sample size.** Power calculations were used to determine the adequacy of sample size, predetermined by total number of eligible children in the study schools and study budget. Using an estimate of difference-in-difference, mean change in Hb of 0.40 (SD 1.2) based on previous studies, adequate sample size need was estimated to be 143 per group [alpha=0.05 and power (1-β=0.80)] (Nga T. et al. 2009). With a design effect of 1.06 applied and an estimated 10% losses to follow-up, the study was found to be adequately powered to detect the hypothesized difference in Hb with 321 children enrolled (Wittes et al. 2002).

**Intervention & Methods.** Students in Group 2 will receive the RUSF/Vita Mamba snack daily for one academic year, 2014-2015. Each RUSF sachet (50g) contains 260 kcal and 100% RDA for most micronutrients. Simple messages about the importance of the RUSF, nutrition, and hygiene will be communicated at a low intensity level in group 2. All children will receive deworming, Albendazole, according to the national protocol of MSPP. Two types of surveys will be developed and administered for data collection in this study.

*Child measures and survey:* Students will be followed longitudinally during the school year on a range of health, nutrition, and education outcomes. A baseline, midline, and endline survey will be administered to assess nutrition and education impacts as well as acceptability of the product, Vita Mamba, to students as part of a school feeding program.

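### A child who reacts to the food leaves the study: a removal after allocation that can occur only in Group 2 and loses that child's endline data (minor)

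*Protocol*

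**What the plan says.** Four places in the protocol bear on this.

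- **Appendix A, Risks.** On timing: "When the fortified peanut-butter paste food is given for the first time, children will be monitored for any adverse reactions". The monitoring lasts one hour and covers skin signs, swelling and breathing trouble. On the consequence: "If a child reacts to the food, they will be treated immediately and become ineligible to continue in the study". The object of that sentence is the study, not the food.
- **Methodology, Study Design.** The control group "will receive no food-based intervention during the study period".
- **Methodology, Intervention & Methods.** "Students in Group 2 will receive the RUSF/Vita Mamba snack daily for one academic year, 2014-2015".
- **Methodology, Sample Schools and Participants.** The exclusion criteria, which apply to both groups, include "Allergy to peanuts or soy".

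On how often a reaction is expected, Appendix A cites a trial of a similar fortified peanut paste: "Among the 410 infants receiving this food, no peanut allergy has been identified".

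Nowhere does the protocol say that a child taken off the food is still measured at endline or kept in the analysis.

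**The concern.** The trigger is exposure to the intervention. Feeding starts only where Vita Mamba has been assigned, so the trigger necessarily follows allocation, and a control child cannot meet it. The screening exclusion balances the groups for allergy that families already know about. It does not balance them for susceptibility that shows itself only when the product is eaten: such a child leaves Group 2, while a counterpart in Group 1 stays and is measured.

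Two things are at stake. First, the groups are no longer compared as allocated, although the protocol presents the trial as a test of effectiveness in a school feeding program that is meant to inform policy. Second, the children who reacted drop out of later observation. Their endline Hb, height and weight (primary outcomes in Appendix C) and morbidity (secondary) are not collected. This is a matter for the protocol rather than the analysis plan, because the rule decides whether the data exist at all.

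**Working it through.** **1. The plan's own figure.** Inputs from the Sample size paragraph: "mean change in Hb of 0.40 (SD 1.2) based on previous studies", alpha 0.05 (taken as two-sided; the text does not say) and power 0.80.

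n per group = 2 × [1.2 × (1.960 + 0.842) / 0.40]² = 141.3, so 142. The plan states 143, so it is reproduced to within one child. The standard error at that size is 1.2 × √(2/143) = 0.14 g/dl.

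**2. Upper limit for the reaction rate.** From 0 of 410, the exact limits are:

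- two-sided 95%: 1 − 0.025^(1/410) = 0.90%
- one-sided 95%: 1 − 0.05^(1/410) = 0.73%

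**3. Children removed at the 0.90% limit.** The protocol does not give the number of children in Group 2, so a range is needed (assumption):

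| Assumed Group 2 size | Basis | Removed at 0.90% |
|---|---|---|
| 107 | one of three equal schools, 321 enrolled | 1.0 |
| 160 | half of 321 | 1.4 |
| 200 | half of about 400 (Abstract) | 1.8 |
| 214 | two of three equal schools, 321 enrolled | 1.9 |
| 267 | two of three equal schools, about 400 | 2.4 |

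The observed rate itself gives 0. A fair summary is 0 to 2 children.

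**4. Shift in the Hb estimate.** If a fraction r is removed and those children differ from the rest by d, the Group 2 mean shifts by r × d.

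- Removed children would have had none of the assumed benefit (d = 0.40): 0.0090 × 0.40 = 0.004 g/dl.
- Removed children differ by a full SD (d = 1.2): 0.0090 × 1.2 = 0.011 g/dl.

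Both are small against a standard error of 0.14 g/dl.

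**5. Power.** With equal groups, the plan's 10% loss and its design effect of 1.06 taken as given, each group has 160.5 × 0.9 = 144.5 children. Power is Φ{0.40 / [1.2 × √1.06 × √(1/n₁ + 1/n₂)] − 1.96}.

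- No removals: 78.6%.
- 0.9% removed from Group 2 only: 78.4%.
- With 400 enrolled: 86.7% and 86.5%.

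**6. Sensitivity to the rate.** The 0 of 410 concerns infants, a similar product and peanut allergy, whereas the rule covers any reaction to the food. Higher rates are shown for range only; they are assumptions and nothing in the protocol supports them. They use 160 children in Group 2 and 321 enrolled.

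| Assumed rate | Removed | Shift, d = 0.40 | Shift, d = 1.2 | Power |
|---|---|---|---|---|
| 2% | 3 | 0.008 g/dl | 0.02 g/dl | 78.2% |
| 5% | 8 | 0.02 g/dl | 0.06 g/dl | 77.5% |

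Even at 5%, with no benefit in any removed child, the shift of 0.02 g/dl is about one-seventh of the standard error (0.02 / 0.14).

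**The case against.** The strongest reply is that the rule will almost never be used. The protocol's own evidence is zero cases in 410, and Appendix A adds that studies in other countries saw no adverse reactions and that Haitian children commonly eat peanut butter without harm. The rule can also be read as a late application of the screening criterion: a child who cannot eat peanut or soy was never in the target population. Finally, analysis sets and safety tables belong in an analysis plan, which is not to hand.

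Much of this stands. The numerical effect is negligible, and the screening exclusion narrows the imbalance to reactions not foreseen at screening. But the late application is made in one group only, because the control group has no feeding at which to discover such children. And while an analysis plan can say who is analysed, it cannot supply an endline measurement that the protocol has stopped.

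A reader might go further and infer that the children lost are those in whom the product failed, so that the benefit is materially overstated. The documents do not support this. The monitoring described is for one hour after the first serving; a child removed then is close to untreated, and nothing links an acute reaction to poor Hb or growth. A reader might also infer that the record of harm is cut short at the reaction itself. That is not shown either: the child is watched and treated, so the reaction is observed, and nothing says that it goes unrecorded. What is lost is follow-up after it.

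**Conclusion.** The point holds as one of principle and is minor. As written, the rule removes children from Group 2 only, after allocation, and ends their follow-up. On the protocol's own figure this is probably 0 to 2 children, about 0.01 g/dl or less on the Hb estimate, and about 0.2 percentage points of power. It gives no ground to doubt the trial's main result.

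This rests on three assumptions: that leaving the study means no endline measurement, which is the plain reading and is contradicted nowhere; that 0 of 410 infants is a usable guide for children aged 3 to 16; and that Group 2 lies within the range of sizes shown above. If the true rate were several times higher, the count would rise, but the effect on the estimate would stay well inside its standard error.

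**What to change.** Leave the treatment of the reaction and the decision about the food exactly as they are, and change only what follows for study participation. Suggested wording for Appendix A:

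> Where consent continues, a child who has reacted to the food remains in the study for endline measurement and is analysed in the allocated group. The reaction is counted and reported.

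This takes no position on any clinical rule. The analysis part can be repeated in the analysis plan; the endline measurement has to be in the protocol.

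The cost is a sentence or two of text and, on the figures above, a few extra endline measurements at schools that the team already visits.

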Appendix B: Privacy and Confidentiality

Privacy

- During the recruitment process, the study team will visit with individuals at the time of school enrollment in a secure place at the school.
- During the consent process, the study team and participants will sit in a secure place such as an empty classroom at the school to ensure that they are appropriately distanced from others for privacy purposes.
- Each child will be measured at a reasonable distance away from the other children to ensure the privacy of the children. The three schools, which will be placed into one of two groups, have been selected so as to prevent contamination between the groups.
- Information collected will pertain to the well-being of the child as relates to the Vita Mamba, the food product. Any information beyond the scope of program evaluation and its acceptance will not be obtained.

Data Collection

- Paper/hard copy records (hard copy surveys, questionnaires, case report forms, pictures, etc.) – Surveys will be stored in a locked box at the Washington University work space in Haiti - Breda, Cap Haitien.
- Electronic records (computer files, electronic databases, etc.) - Only two computer hard drives will contain the names of participants. These computers will also be locked and secured in the Washington University work space in Haiti, Breda, Cap Haitien. Data files will be transferred periodically by jump drive back to the Brown School of Social Work to the computer hard drive of the PI of this study.
- The study team will use the Hemocue system for measuring hemoglobin samples. The disposable microcuvette, which is used to prick the child’s finger, collects a small amount of blood and then mixes it with the reagents immediately. The study team will then place the microcuvette into the portable analyzer, which will report the results on the display. After use, the microcuvettes will be placed in a standard, medical waste container and disposed of properly at the local health center.

Appendix C: Analysis

The primary outcomes tested by the study will be height, weight, and hemoglobin levels of the child, as markers of growth and micronutrient nutrition. The secondary outcomes include: nutrition (weight, diet, and dietary intake); health (morbidities such as diarrhea, and fever). Finally, the study will be examining the feasibility and acceptability of using Vita Mamba in the school feeding context and thus looking at ease of delivery.

The analysis methods will include descriptive and experimental data procedures. Several univariate analyses and multivariate regression analyses will be run to model outcomes and adjust for potential confounding factors. As a longitudinal study, the study will run panel regression by generalized least squared with random effects. Interaction terms will be introduced. As necessary, propensity score matching will be introduced to ensure the two groups are comparable.

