***Vita Mamba* School Feeding Project**

**Study Protocol**

**Abstract**

This study builds on the *Mamba Lespri* School Feeding Project, conducted in Cap-Haitien, 2012-2013, to improve the nutrition of school-aged children, now in a rural context. Our main objective is to test the effect of a locally produced food, Vita Mamba, on reducing anemia and improving growth in school-aged children. The study uses a longitudinal randomized cluster design with three schools assigned to two groups : Group 1: Control (deworming), Group 2: Vita Mamba (and deworming). Schools will be matched on socio-economic, demographic, and nutritional characteristics and randomly assigned to one of the two comparison groups. Approximately 400 Haitian school children ages 3-16 years of age and their parents will be recruited and enrolled to be followed during the 2014-2015 school year. Data will be collected from two groups of participants at each school: children and parents. At baseline, socio-economic and demographic information will be collected from parents. Children will then be followed at two time points: at the beginning (baseline) and end (endline) of the study for nutrition measures (weight and height, and hemoglobin concentration). Parents will be surveyed for socio-economic characteristics, child diet and health, and anthropometry.

**Background and Significance.** The Haitian Ministry of Education has identified poor nutrition as a problem among Haitian school children. Poor nutrition stunts growth and development and compromises the immune system, leaving the body more vulnerable to disease. In Haiti, 20.9% of children less than five years are stunted and 11.4% are underweight (MSPP, 2013), but information about the nutritional status of the school-aged population is limited. One study of Haitian children between the ages of 11 and 19 years showed two-fifths were stunted (Psoter, et al, 2008).

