Before the launch of the pilot study, WUSTL will form the study team, which will review and complete the necessary IRB certification program appropriate for this project. The training will include three (3) components: 1) Technical information and survey administration; 2) protocol instruction for anthropometric and hemoglobin concentration measure; and 3) field testing and validation exercises. The team of enumerators will receive detailed information regarding the product’s ingredients, functionality, and recommended consumption rates. Additional training will be provided to the team to explain the consent process as well as data collection and communication methodologies. Instructions will be given to the team on the correct methodology for conducting the acceptability study.

Intervention Phase.

**Sample Schools and Participants.** The intervention phase of the project will take place during the academic year from September 2014 through June 2015. Selection of the three schools in a communal section of the Great Basin region (Northeast Department) will be based on student socio-economic and demographic information, school size, and current school feeding program. All schools and students have an equitable chance of being included in the study. Three (3) schools will then be matched on important characteristics (basic anthropometry, SES, and school size) and will be assigned to one of two study groups described above: Group 1: Control (Danda); Group 2: Vita Mamba (Dolval).

At each of the three schools, two groups of participants will be part of the study: parents and children. A full description of the study will be provided and they will be invited to participate through the informed consent process. Parents and other caregivers of potentially eligible children will also be contacted at the beginning of the school year. They will be provided with a description of the study and invited to attend one of several meetings at the school with their children. At the meeting, the Study Coordinator will review and provide a full description of the study.

Children of interested parents/caregivers will be screened for eligibility based on the following criteria:

• Children 3-16 years old ;

• Children in good health [no fever, no congenital health condition];

• Children not severely malnourished [weight-for-height Z score >-2];

• Enrollment in the study school for the academic year 2014-2015.

Exclusion criteria are the following:

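### Three schools in two groups cannot support randomization-based inference, and the planned panel regression, read naturally, leaves between-school variation in Hb change out of its p-values

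*Protocol*

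**What the plan says.** The design is described in two ways. The Abstract states: "The study uses a longitudinal randomized cluster design with three schools assigned to two groups", and adds that assignment is random. Methodology, Study Design, opens with "A quasi-experimental evaluation design is planned for this project" and continues at once with "Three primary schools will be matched on socio-economic and demographic factors and randomized into two participant groups". Study Activities repeats the quasi-experimental label.

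Under Sample Schools and Participants, the three schools "will be assigned to one of two study groups described above: Group 1: Control (Danda); Group 2: Vita Mamba (Dolval"). One school is named for each group, and the third is not placed in either.

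Clustering appears once in numerical form, as a design effect of 1.06 in the Sample size paragraph. No ICC is given.

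Appendix C plans regression with confounder adjustment and then: "As a longitudinal study, the study will run panel regression by generalized least squared with random effects". It adds: "As necessary, propensity score matching will be introduced to ensure the two groups are comparable". It does not name the level of the random effect.

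Under Benefits, Appendix A says that the results will show the product to be effective within school feeding, and that the government intends to use them for policy.

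**The concern.** Allocation is by school, and there are only three. A school can differ from another over a year for reasons unrelated to the snack: local illness, harvest, teaching staff, or how deworming was delivered. Where a group is one school, any such difference in Hb change is indistinguishable from the effect of Vita Mamba.

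The only reason Appendix C gives for the random effects is that the study is longitudinal. That points to repeated measures on a child. Such a model takes its standard error from the number of children, so a difference between schools can be reported as a significant treatment effect. Propensity matching of children balances what was measured on children and households. It cannot remove something that happens to a whole school.

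At stake is whether a small p-value can be presented as evidence from a randomized trial and carried into national school-feeding policy.

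**Working it through.** **Inputs from the Protocol (Sample size).** The wording is "mean change in Hb of 0.40 (SD 1.2) based on previous studies", with alpha 0.05, power 0.80, 143 per group, design effect 1.06, 10% loss and 321 enrolled.

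**The plan's own figure.** n per group = 2 × (1.96 + 0.84)² × 1.2² / 0.40², which gives 142 by the normal formula. The t-test version gives 142.2, rounded up to 143. The stated 143 is reproduced with a two-sided test.

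**Inference from the allocation.** Splitting three schools 2:1 can be done in C(3,1) = 3 ways, so the smallest randomization p-value is 1/3. A school-level comparison has 3 − 2 = 1 degree of freedom, with a two-sided 5% critical t of 12.71. If only the two named schools are compared, it has 0 degrees of freedom and no school-level test exists. None of this needs an ICC. For scale, with one school against two and 289 completers, the 1-df test has power of about 16% at ICC 0.0006, 12% at 0.01 and 8% at 0.05, for the planned difference of 0.40.

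**ICC implied by the design effect.** With 321/3 = 107 children per school, ICC = (1.06 − 1)/(107 − 1) = 0.00057, or about 0.0006.

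**Type I error of a test that omits school.** Completers: 321 × 0.9 = 289, or about 96.3 per school if the schools are equal. Equal size is an assumption, because the Protocol gives no school sizes. For one school against two:

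- Variance assumed by the test, in units of SD²: V₀ = 1/96.3 + 1/192.6 = 0.01557.
- True variance: V = (1 − ICC) × V₀ + 1.5 × ICC, where 1.5 = 1 + 1/2.
- Ratio R = V/V₀. Type I error = 2 × [1 − Φ(1.96/√R)].

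For one against one, with all 289 completers in two schools, V₀ = 1/144 + 1/145 and 1.5 becomes 2.

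| ICC of Hb change | R, 1 v 2 | √R (SE multiplier) | Type I, 1 v 2 | R, 1 v 1 | Type I, 1 v 1 |
|---|---|---|---|---|---|
| 0.00057 (implied by 1.06) | 1.05 | 1.03 | 5.6% | 1.08 | 6.0% |
| 0.005 (assumed) | 1.48 | 1.22 | 11% | 1.72 | 13.5% |
| 0.01 (assumed) | 1.95 | 1.40 | 16% | 2.43 | 21% |
| 0.02 (assumed) | 2.91 | 1.71 | 25% | 3.87 | 32% |
| 0.05 (assumed) | 5.77 | 2.40 | 41% | 8.17 | 49% |

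Worked row, ICC 0.01, 1 v 2: R = 0.99 + 0.015/0.01557 = 1.95, and 1.96/1.40 = 1.40, so the two-sided tail is 16%.

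**Would a school term repair this?** No. With two time points, school intercepts remove differences in baseline level, and these already cancel in the change. The problem is variation between schools in the change itself. On change scores, school effects are collinear with group, and three schools are too few to estimate a school variance usefully.

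**The case against.** The best defence is that the plan does not lean on randomization alone. It calls itself quasi-experimental twice, plans confounder adjustment, and allows for clustering in the sample size. At its own design effect the type I error is barely above nominal. An unseen SAP may also specify the random-effect level and the variance estimator.

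Much of this stands, and it limits the point. Some stronger readings are tempting, but the document does not support them:

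- **That the study is in fact non-randomized.** The Abstract and Study Design say that schools are randomized. Naming schools against groups, as in "Group 1: Control (Danda); Group 2: Vita Mamba (Dolval"), is compatible with recording a draw already made. The document shows only that the labels conflict.
- **That the model certainly lacks any school component.** The level is not named. Child level is the natural reading of a two-time-point panel, but it is an inference.
- **That type I error will be 11% to 41%.** Those figures need ICCs that the Protocol does not give, and equal schools.
- **That matching will cost a stated amount of power, or that siblings add a further known error.** No matching ratio or method is given, and there is no sibling count.

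The defence does not reach the structural fact. At least one group is a single school, and no model written in an SAP changes the three allocations or the 1 degree of freedom. The source of the 1.06 is not stated either, so the near-nominal error rate rests on a very small, unsupported ICC.

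**Conclusion.** The point holds in this form and the plan is wrong as written. The randomized and quasi-experimental labels conflict, the third school has no group, and three schools cannot support either randomization-based inference at 0.05 (smallest p-value 1/3) or useful school-level inference (1 degree of freedom, or 0 if two schools are compared). This part needs no assumption beyond the three schools.

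The second part rests on reading the panel as a child-level model. On that reading its p-values and intervals omit between-school variation in Hb change, and propensity matching of children cannot restore it. The excess error ranges from slight at the plan's implied ICC to severe at an assumed 0.05. The Protocol gives no basis for placing the true value within that range. Claiming that the results will establish effectiveness therefore goes beyond what the design can show.

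**What to change.** 1. Reconcile the two design labels throughout. State how the schools were allocated and which group holds the third, and say that allocating three schools cannot support randomization-based inference.
2. Keep the child-level difference-in-difference for Hb, but state that its confidence interval and p-value are conditional on these schools. Beside it, show intervals widened over a range of school ICCs that includes the value of about 0.0006 implied by 1.06. With equal schools, the SE multipliers in the table can be used.
3. Report the change in each of the three schools separately. Use the gap between the two schools in the same group as a descriptive guide only, since one pair is too little for a decision rule.
4. Make propensity matching a sensitivity analysis.
5. In Appendix A, limit the effectiveness statement to a comparison of these schools.

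School fixed effects or household-clustered standard errors should not be offered as a remedy, because neither captures school-specific change.

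The cost is wording, one extra table and a short sensitivity analysis, with no new data. The price is weaker conclusions and wider stated uncertainty.
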